### Data acquisition and assessment of biological data

Participants receive a study ID, which is used to conceal their identity in documents. Investigators involved in this study have access to their actual identity only on an as-needed basis.

The recruitment rate is the percentage of eligible patients who agree to participate in the study. The dropout rate is the percentage of patients who are lost after enrollment up to the 28th day from enrollment, after which no outcome data are collected. Follow-ups are by bedside visit if the patient is still in hospital, or by phone call when a face-to face follow up is not available.

As well as the outcome measures, the following clinical data will be collected from all participants: age, gender, infection source, and co-morbidities. Immune function data, inflammation data, APACHE II scores, and SOFA scores will be collected on the day of enrollment and 3 days after enrollment. The trial schedule is listed in Fig. 2.

**Fig. 2 Fig2:**
[figure not shown]
Standard Protocol Items: Recommendations for Interventional Trials (SPIRIT) timeline of measurements. Laboratory examination includes the immune function data (mHLA-DR expression, ratio of CD4+ to CD8+ T lymphocytes), inflammation data (C-reactive protein, interleukin-6, interleukin-10, PCT and TNF-α), complete blood count (CBC), general urine analysis, liver function tests (ALT, AST, ALP, TBIL, and GGT), renal function test (BUN and Scr). ALT alanine transaminase, ALP alkaline phosphatase, AST aspartate transaminase, BUN blood urea nitrogen, CBC complete blood count, GGT gamma-glutamyltransferase, mHLA-DR monocyte human leukocyte antigen-DR, PCT procalcitonin, TBIL total bilirubin, TNF-α Tumor necrosis factor α, Scr serum creatinine,SNT Si-Ni-Tang,SPIRIT Standard Protocol Items: Recommendations for Interventional Trials

All mHLA-DR measurements are done in the central laboratory of Guangdong Provincial Academy of Chinese Medical Sciences by flow cytometry (FC-500; Beckman Coulter, Inc., USA) within 4 h after the blood draw. First, 100 μL of unprocessed ice-stored peripheral whole blood sample (anticoagulated with EDTA-K2) will be added to 10 μL of HLA-DR-FITC (clone L243, eBioscience, Inc. SanDiego, CA, USA), CD14-PE (clone 61D3, eBioscience, Inc., San Diego, CA, USA) and CD45-PC5 (clone HI30, eBioscience, Inc. SanDiego, CA, USA) separately. Negative control antibodies are used as follows: Mouse IgG1 K Isotype Control PE (eBioscience, Inc. SanDiego, CA, USA), Mouse IgG1 K Isotype Control PE-Cyanine5 (eBioscience, Inc. SanDiego, CA, USA) and Mouse IgG2a K Isotype Control FiTC (eBioscience, Inc. SanDiego, CA, USA). CD14+ monocytes will be characterized, and 2000–5000 monocytes will be collected. The number of HLA-DR+ monocytes out of the total monocyte population will be recorded as a percentage.

IL-6, IL-10, and TNF-α will be measured with an additional 2–3 mL of peripheral venous blood using ELISA kits (Cusabio, CSB-E04638h; Cusabio, CSB-E04593h; Cusabio, CSB-E04740h). The serum will be separated by centrifugation at 3000 rpm for 20 min and stored at −80 °C for the final analysis. Repeated freezing and thawing will be avoided.

Routine laboratory examinations of complete blood counts, general urine analysis, CRP, liver function tests (ALT, AST, ALP, TBIL, and GGT), and renal function tests (BUN and Scr) will be done by the clinical laboratory of Guangdong Provincial Hospital of Chinese Medicine.

Researchers are trained to collect trial data carefully according to a standard protocol. Molecular biomarkers will be measured in triplicate to ensure quality. All data will be input into an electronic database (REDCap 5.7.0, hosted at Peking Union Medical College Hospital) designed for the study. The data will be entered independently into the database by two researchers and will be checked separately by different trained researchers. All collected data forms will be kept in the hospital’s Scientific Research Department.

All adverse events after enrollment to the 28th day after enrollment, regardless of whether they are related to the intervention, will be recorded. All severe adverse events and unexpected adverse events will be reported to the ethics committee within 1 day. The intervention will be suspended if necessary. Symptomatic treatment will be offered when needed. The principal investigator will decide whether patients affected by adverse events should discontinue their participation.

Data and safety will be monitored by the institutional review board of Guangdong Provincial Hospital of Chinese Medicine and the Scientific Research Department of Guangdong Provincial Hospital of Chinese Medicine, which are independent of the sponsor and have no competing interests.

### Statistical analysis

Quantitative numerical data with a normal distribution will be presented as mean ± standard deviation, while data with a non-normal distribution will be presented as median and interquartile range. Categorical variables will be expressed as frequencies or numbers. Equality of variances between groups will be assessed by Levene’s test. An unpaired Student’s *t*-test will be used for normally distributed quantitative variables, while the Wilcoxon nonparametric statistic will be used for non-normally distributed variables. Pearson’s chi-squared test or Fisher’s exact test will be used for categorical data when appropriate. Differences in biological metrics between arms over time will be evaluated by repeat measures of a general linear model, if appropriate. An intention-to-treat analysis will be used for data for participants who did not complete the study or the follow-ups after treatment.

*P <* 0.05 will be considered as statistically significant. All statistical analyses will be performed with SPSS (version 17.0, Chicago, USA) for Windows by researchers not involved in implementing the trial.

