### Outcomes

The primary endpoint is the feasibility of the study. It will (1) explore the feasibility of recruiting, randomizing, and retaining participants, (2) evaluate the acceptability and compliance of SNT as an intervention alongside usual care, (3) evaluate the appropriateness of secondary outcome measures, (4) generate data for effect size calculations for future trials, and (5) be used to develop an appropriate protocol for further trials. The time required to recruit 50 participants, the recruitment rate, and the dropout rate will be measured. Successful recruitment is defined as at least half (50%) of eligible patients enrolled, with a dropout rate of no more than 20%.

The secondary endpoints include:
28-day all-cause mortality ratesimmune function data: monocyte human leukocyte antigen-DR (mHLA-DR) expression and ratio of CD4+ to CD8+ T lymphocytesinflammation data: CRP, interleukin-6 (IL-6), interleukin-10 (IL-10), procalcitonin, and tumor necrosis factor α (TNF-α) levelsSequential Organ Failure Assessment (SOFA) scoresAcute Physiology and Chronic Health Evaluation (APACHE) II scores

The exploratory outcomes are mortality in the ICU, length of stay in the ICU, hospital mortality, and length of hospital stay. Safety outcomes include a complete blood count, a general urine analysis, C-reactive protein (CRP), liver function tests (alanine transaminase (ALT), aspartate transaminase (AST), alkaline phosphatase (ALP), total bilirubin (TBIL), and gamma-glutamyltransferase (GGT)), and a renal function test (blood urea nitrogen (BUN) and serum creatinine (Scr)), all of which will be performed at days 0 and 3.

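### Biomarkers and scores are measured at day 0 and day 3, but the plan names no comparison of arms that adjusts day 3 for day 0, and so gives up precision it could have at no cost

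*Protocol article*

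**What the plan says.** The section on data acquisition fixes two measurement times: "Immune function data, inflammation data, APACHE II scores, and SOFA scores will be collected on the day of enrollment and 3 days after enrollment". The Outcomes section sets the same two days for the safety laboratory tests.

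The Statistical analysis section names the methods for comparing arms:

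- For quantitative variables in general: "An unpaired Student’s *t*-test will be used for normally distributed quantitative variables", with the Wilcoxon test where the distribution is not normal.
- For repeated biological measures: "Differences in biological metrics between arms over time will be evaluated by repeat measures of a general linear model, if appropriate".
- For non-completers: "An intention-to-treat analysis will be used for data for participants who did not complete the study or the follow-ups after treatment".

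No comparison is described in which the day-0 value enters as a covariate. The Sample size section asks for at least 20 participants per group so that the next trial can be sized with enough precision, and plans 50 in total after a 20% dropout allowance. The Outcomes section lists supplying effect sizes to later trials among the aims of the feasibility endpoint.

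**The concern.** The baseline value of each marker and score is already being collected, and it usually carries information about the day-3 value. Neither named method makes the best use of it. A t or Wilcoxon test on day-3 values would ignore it. A repeated-measures model with only two visits subtracts it with a fixed weight of one, whatever the actual correlation between visits.

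What is at stake is precision in a trial whose sample size is justified by precision. With about 20 evaluable patients per arm the intervals will be wide, and the estimates are meant to inform the design of a larger trial.

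A second, smaller matter is patients without a day-3 value. A classical repeated-measures model and a day-3 test use only patients who have that value, unless something is imputed. The named methods therefore do not by themselves deliver the stated intention-to-treat analysis.

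**Working it through.** **The plan's own figure.** 20 per arm is 40 evaluable patients; 40 / (1 − 0.20) = 50. This reproduces the stated total. The article states no power or effect-size calculation, so there is none to check.

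**Inputs.** From the document: two visits (day 0 and day 3), 1:1 allocation, 20 evaluable per arm. Assumed, because the documents do not give them: a day 0–day 3 correlation ρ of 0.3, 0.5 or 0.7, and equal SDs at the two visits.

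**What the two-visit model tests.** The sentence on the model speaks of differences between arms over time, which points to the group-by-time term. With two visits that term is the difference between arms in mean (day 3 − day 0), so its test is a t-test on change scores.

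**Variance of the estimated arm difference, relative to a day-3-only comparison:**

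- day-3 values only: 1
- change score: 2(1 − ρ)
- ANCOVA on day 0: 1 − ρ²

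ANCOVA relative to change score is (1 − ρ²) / [2(1 − ρ)] = (1 + ρ)/2.

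| ρ | ANCOVA ÷ change score | 20 per arm acts like | ANCOVA ÷ day-3 only | 20 per arm acts like |
|---|---|---|---|---|
| 0.3 | 0.65 | 20/0.65 ≈ 31 | 0.91 | 20/0.91 ≈ 22 |
| 0.5 | 0.75 | 20/0.75 ≈ 27 | 0.75 | 20/0.75 ≈ 27 |
| 0.7 | 0.85 | 20/0.85 ≈ 24 | 0.51 | 20/0.51 ≈ 39 |

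**95% CI half-width in SD units**, 1.96 × √(2v/20), where v is the relative variance:

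| ρ | Day-3 only | Change score | ANCOVA |
|---|---|---|---|
| 0.3 | 0.62 | 0.73 | 0.59 |
| 0.5 | 0.62 | 0.62 | 0.54 |
| 0.7 | 0.62 | 0.48 | 0.44 |

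**Unequal SDs.** Write σ₀ and σ₃ for the SDs at day 0 and day 3. The change-score variance minus the ANCOVA variance is σ₀² + σ₃² − 2ρσ₀σ₃ − σ₃²(1 − ρ²) = (σ₀ − ρσ₃)², which is never negative. The size of the gain depends on the equal-SD assumption; its direction does not.

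**Price of the covariate.** Estimating the slope inflates the variance by about 1 + 1/(2n − 4), which is 37/36 ≈ 1.03 at n = 20 per arm. Against a day-3-only test, ANCOVA breaks even where 1 − ρ² = 36/37, that is at ρ ≈ 0.16. Below that the loss is at most about 3%.

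**Missing day-3 values.** In 3,000 simulated trials with 25 per arm and about 20% of day-3 values missing, the day-3 test, the change score and ANCOVA all rested on about 40 of the 50 patients. When control patients with low day-0 values were more often missing, a true difference of 0.50 SD was estimated at ρ = 0.5 as 0.37 (day-3 test), 0.63 (change score) and 0.50 (ANCOVA). Day-0 adjustment removes bias that depends on baseline. It does not bring the missing patients back into the analysis.

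**The case against.** The strongest reply is that a change-score analysis in a randomised trial is valid and unbiased, that the repeated-measures model already uses day 0, and that these outcomes are secondary in a pilot whose Discussion concedes it may not detect an effect. All of this stands. It makes the point one of efficiency, and the gain over the change score narrows as ρ rises: 15% of the variance at ρ = 0.7. It does not remove the point, because the methods are stated choices and precision for the next trial is a stated purpose.

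Three stronger readings are tempting, and the article supports none of them.

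- *That patients without day-3 data are dropped, contrary to intention to treat.* The article nowhere says so; it promises the opposite. Deletion is the default of the named methods when nothing is imputed. The rule for missing values may stand in an analysis plan that is not shown.
- *That two competing analyses are named for the same endpoints.* The t and Wilcoxon tests are assigned to quantitative variables in general, which include age and lengths of stay. The natural reading keeps the repeated-measures model for the biological measures. The wording is loose: the condition attached to the model is not explained, and it is unclear whether SOFA and APACHE II count as biological metrics. Looseness is not a contradiction.
- *That adjustment nearly doubles the effective sample.* The figure of 39 per arm holds only against a day-3-only test at ρ = 0.7, and the article never assigns such a test to the biomarkers.

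**Conclusion.** The point holds as an efficiency recommendation. The plan collects day-0 values for every immune marker, inflammation marker and severity score, yet names no comparison that conditions on them.

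Against the two-visit repeated-measures model, ANCOVA cuts the variance by 35%, 25% or 15% at ρ = 0.3, 0.5 or 0.7. Against a day-3-only test, if that is what the t or Wilcoxon test would be, the cut is 9%, 25% or 49%. These sizes rest on an assumed correlation and on equal SDs at the two visits, neither of which the documents give.

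On missing day-3 values the supportable statement is limited: the named methods need a missing-data rule, or a model that accepts incomplete pairs, before they can support the intention-to-treat statement. The feasibility endpoint is not affected.

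**What to change.** In the Statistical analysis section, replace the unadjusted tests and the repeated-measures model with one analysis for mHLA-DR, CD4/CD8, CRP, IL-6, IL-10, procalcitonin, TNF-α, SOFA and APACHE II: ANCOVA of the day-3 value on arm, with the day-0 value as covariate, on the log scale for skewed markers. Report the adjusted difference with its 95% CI, and pass that estimate to the effect-size calculations for the later trial.

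ANCOVA alone also omits patients without a day-3 value. To support the intention-to-treat statement, fit the equivalent linear mixed model to both visits with a common baseline mean for the two arms. Say that this assumes missingness depends only on the observed data. Report deaths before day 3 separately by arm, since no model supplies a meaningful day-3 value for them.

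The t and Wilcoxon tests can stay for quantities without a baseline value, such as length of stay.

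Cost: a change of wording, one degree of freedom per analysis and a little analysis work. No new data are needed.

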**Methods/design:**

This is a pilot randomized controlled study. Eligible sepsis patients admitted to our medical intensive care unit will be randomly allocated to the control group or the SNT group. Both groups will receive standard therapy according to the recommendations of the Surviving Sepsis Campaign. In addition, the SNT group will receive SNT (150 mL per day for 3 days) orally or by gastric tube, while the control group will receive 150 mL of normal saline. The primary outcome is to assess the feasibility of this treatment. The secondary outcomes include: (1) immune function measured by monocyte human leukocyte antigen-DR (mHLA-DR) expression, procalcitonin, and the ratio of CD4+ to CD8+ T lymphocytes and (2) other clinical data, such as the 28-day all-cause mortality, Sequential Organ Failure Assessment (SOFA) scores, Acute Physiology and Chronic Health Evaluation (APACHE) II scores, both of the latter on days 0 and 3.

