SNT, a classical herbal formula, has been used for the collapse stage of severe diseases including sepsis in China for thousands of years. It restores *yang* and its warming effect dispels cold [9]. It may have therapeutic effects in patients and animals with sepsis, such as alleviating an inflammatory response [11, 12], ameliorating microcirculatory disturbances [13], and improving shock reversal [14]. However, the effects of SNT on immune function in sepsis have never been investigated. To our knowledge, the present pilot study is the first clinical trial to explore the potential underlying molecular mechanisms and changes in immune function in sepsis due to SNT. The results of this pilot trial may provide insights into the feasibility of a large-scale trial on SNT applied as an adjunctive immunostimulating therapy for a specific subgroup of sepsis patients.

There are several limitations to this pilot study. First, the trial does not have an oral placebo control. When the experimental drug is in the form of granules and powders, an oral placebo can be produced with the same appearance and odor. However, a placebo decoction prepared with distilled water and food coloring to resemble SNT would not have the same smell and taste as the experimental decoctions used in this study. Also, *zhigancao*, a commonly used herb, could not be boiled and used as a placebo decoction alone, since it has a specific pharmacological effect in restoring *qi*. Hence, there is no oral placebo.

Second, this is a pilot trial with a small sample size. The participants are not blinded, and the treatment sepsis patients received is complicated. Hence, this study may not be able to find a significant therapeutic effect.

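### A feasibility pilot sized for precision applies one unqualified P < 0.05 rule to 14 secondary and exploratory outcomes; estimates with confidence intervals would serve its stated aims better

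*Protocol article*

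**What the plan says.** All references are to the protocol article.

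- **Outcomes.** "The primary endpoint is the feasibility of the study". The success criterion is: "Successful recruitment is defined as at least half (50%) of eligible patients enrolled, with a dropout rate of no more than 20" per cent. One of the listed feasibility aims is to supply effect-size data for later trials; another is to judge whether the secondary outcome measures are suitable.
- **Outcomes, secondary.** Ten measures: 28-day mortality, mHLA-DR, CD4+/CD8+ ratio, CRP, IL-6, IL-10, procalcitonin, TNF-α, SOFA and APACHE II.
- **Outcomes, exploratory.** Four measures: "The exploratory outcomes are mortality in the ICU, length of stay in the ICU, hospital mortality, and length of hospital stay".
- **Sample size determination.** At least 20 per group, justified by precision for a later sample size calculation. Allowing for 20% dropout, the total is 50.
- **Statistical analysis.** Descriptive summaries by arm; t-test or Wilcoxon according to distribution; chi-squared or Fisher for categorical data; a repeated-measures general linear model for biological metrics over time, where appropriate. Then the rule: a P value below 0.05 "will be considered as statistically significant". Nothing limits it to particular outcomes or labels the tests descriptive.
- **Discussion.** The authors concede that "this study may not be able to find a significant therapeutic effect".

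**The concern.** The significance rule serves none of the trial's stated objectives. Feasibility is judged on recruitment and dropout, and the sample was not chosen to test any effect. Followed as written, the rule would still attach the label of statistical significance to any of 14 outcomes that crosses 0.05.

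Two things are at stake. First, with this many outcomes, at least one crossing by chance is far more likely than 5%. Second, and whatever the correlation between outcomes, a small trial reaches P < 0.05 only when the observed difference is large. Effects singled out because they were significant therefore tend to be too big. A full trial sized on such a marker would be too small. In the other direction, a useful marker could be set aside because it missed 0.05 in a trial with little power to reach it.

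**Working it through.** **Inputs.** From the article: threshold 0.05; 10 secondary and 4 exploratory outcomes; 20 per group before dropout; 20% dropout; 50 in total; 1:1 allocation. Assumed, because the article is silent: two-sided tests, the correlations between outcomes, and the true effects used for illustration.

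**Step 1. The plan's own figure.** 2 × 20 / (1 − 0.20) = 40 / 0.80 = 50. This reproduces the stated total.

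**Step 2. Chance of at least one P < 0.05 with no true effect, independent outcomes.**

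- Either direction, 10 secondary outcomes: 1 − 0.95^10 = 40.1%.
- Either direction, all 14: 1 − 0.95^14 = 51.2%.
- Favouring SNT only (0.025 per test), 10 outcomes: 1 − 0.975^10 = 22.4%.
- Favouring SNT only, all 14: 1 − 0.975^14 = 29.8%.

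**Step 3. The same with correlation.** The list overlaps heavily: three mortality measures, two lengths of stay, five inflammation markers, two severity scores. Simulating 14 normal test statistics with a common assumed correlation gives:

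| Assumed correlation | Either direction | Favouring SNT only |
|---|---|---|
| 0 | 51% | 30% |
| 0.2 | 47.5% | 25.0% |
| 0.3 | 44.0% | 22.5% |
| 0.5 | 35.0% | 17.5% |
| 0.7 | 24.8% | 12.4% |

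With correlation stronger within related groups of outcomes than between them (again assumed values), the results are 37–45% in either direction and 19–24% favouring SNT. If Fisher's test, which is conservative at this size, is used for the mortality outcomes, they fall to about 35–41% and 18–22%.

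**Step 4. What a significant result looks like with 20 per arm.** The smallest observed standardised difference that reaches P < 0.05 in a t-test is t(0.975, 38 df) × √(2/20) = 2.024 × 0.316 = 0.64 SD. Power is 34% for a true difference of 0.5 SD; 80% power needs 0.91 SD.

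**Step 5. Exaggeration after selection.** In simulated normal data with 20 per arm, results that reach P < 0.05 overstate a true effect of 0.5 SD by about 1.7-fold and one of 0.3 SD by about 2.6-fold. Required sample size varies with 1/effect². A trial planned on a 1.7-fold overstatement would therefore have about 1/1.7² = 0.35 of the participants it needs.

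**Step 6. Precision of the feasibility result.** Exactly 10 dropouts among 50 (20%, the limit of the success criterion) has an exact 95% confidence interval of 10.0% to 33.7%. An observed rate on the limit is compatible with true rates well to either side of it.

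**The case against.** The strongest reply is that this is a routine sentence in a condensed article. Secondary and exploratory outcomes of a pilot do not usually need a multiplicity correction. Confidence intervals and the labelling of P values can be left to an analysis plan that is not shown. No trial decision depends on these tests, because the success criterion uses none. The article frames its aim as feasibility throughout, and its Discussion already warns of the small sample.

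Much of this stands. No correction is called for, the absence of confidence intervals would not be a point by itself, and the power figures in part restate what the authors disclose. What remains is the rule the article does state: it is unqualified and does not fit the stated aims. The Discussion warns that a real effect may be missed; it does not warn that a significant one may be chance or inflated.

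Four stronger readings are tempting, and the article does not support them:

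- **A false efficacy signal is as likely as not.** The 51% requires 14 independent outcomes and counts differences in either direction, including harm. The outcomes plainly overlap, and a false signal favouring SNT is about 12–30%. For IL-6, IL-10 and TNF-α the article fixes no direction of benefit, so counting both directions is reasonable for those markers, but not for mortality or severity scores.
- **Every outcome can be tested twice.** The t-test and Wilcoxon are alternatives chosen by distribution. Only the biological metrics can also go into the general linear model, and only where appropriate.
- **The analysis consists of significance tests alone.** The section also specifies means, medians, spreads and frequencies, and the Outcomes section commits to measuring recruitment and dropout.
- **Non-significance will be taken as no effect.** The Discussion's own limitation speaks against that.

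**Conclusion.** The point holds as a mismatch between a stated decision rule and the stated purpose of the trial. Under no true effect, at least one of the 14 outcomes would be called significant with a probability of 51% if independent and roughly 25–48% if correlated at 0.2 to 0.7. For signals favouring SNT the figures are about 30% and 12–25%. These rest on two-sided testing and on correlations that the article does not give, so they are a range and not an estimate. The 0.64 SD threshold does not depend on those correlations; it assumes a t-test with 20 analysed per arm. The consequence is limited: the feasibility decision is unaffected, and the risk lies in how outcome results are labelled and then carried into planning the full trial. It rates as a cheap improvement, not as a flaw that undermines the pilot.

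**What to change.** Replace the P < 0.05 sentence in the Statistical analysis section with a statement to this effect: secondary and exploratory outcomes are reported as between-arm estimates with 95% confidence intervals; any P values are descriptive; no conclusion about efficacy is drawn from the pilot. Add that the recruitment and dropout rates, as the main results, are reported with exact 95% confidence intervals beside the 50% and 20% criteria. Do not add a multiplicity adjustment: Bonferroni over 14 outcomes would mean 0.05/14 = 0.0036 per test, which with about 20 per arm leaves little power and serves no aim of the pilot.

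The cost is wording only, with no added participants, measurements or visits. The article reports that recruitment is under way, so the change can be made before analysis. The sponsor gives up the option of claiming a significant biomarker effect from this trial.
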